#### 2.8.1. Loss to Follow-Up, Compliance, and Missing Data

Based on previous experiences, we expect approximately 60% of the total workforce at the plants to volunteer for participation in the project. The project will be deeply anchored with the plant’s leadership. Participants will be closely followed by the Occupational Health Service after inclusion, and we expect 10–20% loss to follow-up for the whole 3-year period. For the intervention group, 80–90% compliance is expected for the planned and supervised sessions. Outcome will be censored in case of people leaving the employment at the plants due to unemployment, disability pension, or rehabilitate pension. Missing outcome values will be taken into account by the mixed model approach, and no prior imputation is necessary. For the adjustment variables, we do not expect much missingness.

#### 2.8.2. Study Power

Based on the assumption of 60% participation, we expect approximately 125 participants at baseline. Furthermore, our power calculation assumes a dropout of 10% after one year, and 20% after three years.

We consider the first research question as the primary one, and to evaluate statistical power, we focused on the effect of shift work on change in systolic blood pressure from baseline to last follow-up. We fixed the between-subject and within-subject variability to values estimated in a similar longitudinal study [37], i.e., we assumed a between-worker standard deviation of 9.3 and a within-worker standard deviation of 7.8. Furthermore, we assumed an effect size corresponding to a yearly increase of 1.5–2 units in blood pressure in the shift group compared with the reference group of day workers. Based on these assumptions, we obtained a power of 0.56–0.80 of getting a significant effect of shift work on change in systolic blood pressure. However, to better account for the fact that we have multiple outcomes, we took this power analysis one step further. We assumed that of the variables included in our study, 1/3 had an effect size of the same magnitude as for the systolic blood pressure, while for the other 2/3 of the outcomes, we assumed there were no effects of shift-work exposure. We adjusted the *p*-values for multiple-testing using a Bonferroni correction and obtained a power of 0.57–0.95 of getting at least one significant finding when adjusted for multiple testing.

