### 2.8. Statistical Analyses

The statistical analyses will address the four research objectives stated earlier.

To elucidate the first objective, we will study the effect of shift-work on CVD-risk outcomes during a three-year follow-up using measurements at baseline and at the one- and three-year follow-ups. The primary comparison will be between the three-year follow-up and baseline. The exposure variable will be dichotomous with categories “shift-worker” and “day-worker” (reference category).

For the second research objective, we plan to use objectively measured sleep and subjectively measured sleep quality during the five-week shift period as continuous exposures variables and investigate associations to CVD risk factors. We will also include an analysis where sleep is considered a mediator between shift-work and CVD outcomes.

The third research objective concerns the effect of a three-month scheduled plant shutdown on CVD-risk outcomes. Measurements will be done before and after the shutdown, and we aim to investigate possible changes in this period.

The fourth research objective studies the effect of an eight-week HIIT intervention. We will look at the change in CVD-risk outcomes for the intervention group, and also compare this to the corresponding change for the control group. In addition to this intention to treat type analysis, we plan also to do a per-protocol analysis, where only persons having attended at least 40 percent of the training sessions will be counted as part of an HIIT group. The remaining persons will be considered to be part of the control group. We will also measure their degree of physical activity during the eight-week follow-up using the PAI index, and we will investigate whether this measure is associated with changes in the CVD-risk outcomes.

All the research questions involve longitudinal data with two or more time points. Linear and logistic mixed models will be used for all research questions. For the continuous outcomes, a linear mixed model will be used to analyze the data with a random intercept for worker, and adjustment for age, gender, and smoking. For the dichotomous outcomes, a logistic mixed model will be used with the same random-effect and fixed-effect variables. To control for multiple testing, we will use *q*-values, which is the false discovery rate equivalent for *p*-values [36].

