The prospective design is favorable, and three years is a considerable follow-up time. However, the development of e.g., cIMT is a slow process, and even though changes in cIMT were found in diabetes and coronary patients after a 12-month exercise program [56], the follow-up period may be too short to detect changes, even for subjects in a worsening state. Additionally, at the time of our investigation, many of the workers will have several years of shift work behind them, which may have, in addition to a “healthy worker effect”, an impact on further changes in some of our measures. Thus, we will strive to account for seniority in shift-work in our analyses. There is also a possibility that males and females respond differently to the circadian misalignment occurring during shift work [57], and we will strive to account for this in our analyses. However, we do not aim to investigate this issue separately in our study, and it is unlikely that we will have the optimal data set to do so, considering the male domination of workers in this occupational sector. With a follow-up period of three years, we cannot ignore the possibility of drop-outs during this part of the project. It is also of importance that participants in subgroups of PA intervention and sleep monitoring stay motivated throughout the periods of intervention and continuous measurement. Designated motivators and the involved physiotherapist from the occupational health service will be present during exercise sessions and in regular contact with all the participants. There will also be regular meetings between representatives from the participating enterprises and the project group during the three-year follow-up. This could improve compliance and limit loss to follow-up. From the sample size calculations, we regard a total sample size of 125 subjects as being large enough to show effects, even when considering a reasonable drop-out of participants.

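### The 0.56–0.80 power for systolic blood pressure belongs to an unadjusted 5% test; the plan tests it by q-value, and its power under that rule is not given

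*Protocol article*

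**What the plan says.** All of this is in the protocol article.

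- **Section 2.8.2, inputs.** On numbers, the authors write: "we expect approximately 125 participants at baseline". On attrition, the text reads: "our power calculation assumes a dropout of 10% after one year, and 20% after three years". On variability, it says: "we assumed a between-worker standard deviation of 9.3 and a within-worker standard deviation of 7.8". The effect is set at 1.5–2 units per year more in shift workers than in day workers.
- **Section 2.8.2, sBP.** The result for this outcome is stated thus: "we obtained a power of 0.56–0.80 of getting a significant effect of shift work on change in systolic blood pressure". No significance level is printed.
- **Section 2.8.2, multiplicity.** The authors then suppose that one third of the outcomes carry an effect as large as that on sBP and the rest none. The correction and its result are given as: "using a Bonferroni correction and obtained a power of 0.57–0.95 of getting at least one significant finding when adjusted for multiple testing".
- **Section 2.8, analysis.** The method named is the q-value, in a sentence that opens "To control for multiple testing, we will use". It closes the description of models for all research questions and makes no exception.
- **Primary status.** Section 2.8.2 calls the first research question primary, and Section 2.8 makes three years versus baseline the primary comparison. Neither names a primary outcome; sBP is the variable chosen to evaluate power.
- **Strengths and Limitation.** With reference to the power work, the authors conclude: "we regard a total sample size of 125 subjects as being large enough to show effects, even when considering a reasonable drop-out of participants".

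**The concern.** The article gives two power figures, and neither describes the planned test of sBP. The first leaves out the multiplicity rule. The second includes a multiplicity rule, but a different one (Bonferroni instead of q-values), and it answers a different question (any outcome instead of sBP). A q-value rule at a conventional threshold asks more of the sBP p-value than 0.05, so the power for sBP falls.

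At stake is how the main result is read. The discussion calls 125 subjects enough, although the lower printed figure is only 0.56 before any adjustment. A reader who takes that statement at face value could give a non-significant sBP result more weight than the design supports.

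**Working it through.** **1. Inputs from the documents.** 125 workers; visits at 0, 1 and 3 years; dropout 10% at one year and 20% at three; between-worker SD 9.3, within-worker SD 7.8; random-intercept linear mixed model. The effect is 1.5–2 units a year, so 3 × 1.5 = 4.5 to 3 × 2 = 6 units over three years.

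**2. Inputs I had to assume.** Two-sided 0.05, and equal groups. Section 2.5 lists 51 + 55 = 106 eligible shift workers and Section 2.1 lists 213 employees; 106/213 = 0.50, so 1:1 is reasonable.

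**3. Reproducing 0.56–0.80.** Power ≈ Φ(Δ/SE − 1.96), with SE from generalised least squares under the random-intercept model and monotone dropout.

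| Model for time | SE of 3-year difference | Δ/SE | Power |
|---|---|---|---|
| Linear | 2.126 | 2.117; 2.822 | 0.562; 0.806 |
| Visit contrast | 2.147 | 2.096; 2.795 | 0.554; 0.798 |

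Hand check on change scores: SD of change = 7.8 × √2 = 11.03; completers per group = 125 × 0.8 / 2 = 50; SE = 11.03 × √(2/50) = 2.206; power 0.532 and 0.776. The printed range is thus an unadjusted 5% figure with about equal groups. A 60:40 split would give 0.545–0.789 with linear time.

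**4. Size of the family.** The article gives no count. The baseline and three-year measures in Sections 2.4.2–2.4.7 come to about 23: 5 routine blood tests, 7 cytokines and adipokines, 3 for sBP, diastolic pressure and resting heart rate, 4 for central pressure and stiffness, 3 carotid measures, and VO2max. I used 20–24.

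**5. sBP power under q-values.** Powers of 0.56 and 0.80 correspond to non-centralities of 2.11 and 2.80. I simulated vectors of m z-statistics, about one third with that non-centrality, and counted how often sBP was declared significant. The Benjamini-Hochberg (BH) q-value is the minimum over j ≥ i of m·p(j)/j. The Storey q-value multiplies this by the estimated null share, #{p > 0.5}/(0.5·m).

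| FDR | Outcomes; correlation | Estimator | 1.5 units/yr | 2 units/yr |
|---|---|---|---|---|
| Unadjusted 5% | – | – | 0.56 | 0.80 |
| 5% | 20–24; 0–0.3 | BH | 0.26–0.29 | 0.58–0.61 |
| 5% | 20–24; 0–0.3 | Storey | 0.32–0.35 | 0.64–0.69 |
| 10% | 21; 0.3 | BH | 0.39 | 0.70 |
| 10% | 21; 0.3 | Storey | 0.47 | 0.78 |
| 20% | 21; 0.3 | BH | 0.53 | 0.82 |
| 20% | 21; 0.3 | Storey | 0.63 | 0.89 |

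A correlation of 0.5 changes the 5% rows by about 0.01–0.03.

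**6. Plausibility check by hand.** Under BH with 21 outcomes and k rejections, sBP needs p ≤ 0.05·k/21.
- k = 3: cut-off 0.0071, z = 2.69, Φ(2.11 − 2.69) = 0.28.
- k = 5: cut-off 0.0119, z = 2.515, Φ(2.80 − 2.515) = 0.61.

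Both agree with the simulation.

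**7. Sensitivity at 5% FDR, BH.** With only 10 or 15 outcomes, power is 0.29–0.31 to 0.59–0.61, so the exact count matters little. If sBP were the only true effect among 20 outcomes, power would be 0.19 to 0.42.

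**The case against.** **The figure is not wrong.** This stands. 0.56–0.80 is correctly calculated, and a reader who infers an arithmetic error would be mistaken. The article does not present it as adjusted, and the next sentences take up multiplicity openly. The fault is that no figure matches the planned test of sBP.

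**No single reduced power follows from the plan.** This also stands. It is tempting to say that the design really delivers 0.26–0.60. That needs a 5% FDR, the BH estimator and some 20 outcomes, and the article fixes none of these; only the one-third share is its own. An article may leave such details to the analysis plan. Storey q-values or a looser FDR raise the figure, and at 20% the loss is small or absent. The reduced figures must stay conditional.

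**The 0.57–0.95 range cannot be faulted on this evidence.** A reader might infer that it is not reproducible, or that 0.95 is out of reach. Both inferences depend on correlations that the article does not state. With 15 outcomes under Bonferroni, 1.5 units a year at correlation 0.3 gives about 0.58, and 2 units a year under independence gives 0.95. Using Bonferroni here is also slightly conservative: whenever it rejects something, BH at the same level does too.

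**sBP is only the worked example, and sufficiency is only a discussion remark.** Partly right: the first question covers cardiovascular risk outcomes in general, and making sBP primary is one option rather than a requirement. But the remark on sample size rests explicitly on the power calculations, and those do not cover the planned sBP test.

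**Conclusion.** The point holds in a limited form. The stated sBP power applies to an unadjusted two-sided 5% test with about equal groups, which is not the test that Section 2.8 describes. The adjusted figure concerns any outcome under another procedure, so it does not fill the gap.

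At a 5% FDR, with about 20–24 outcomes and one third true effects, the shortfall against 0.56 at the smaller effect is about 0.27–0.30 with BH (0.56 − 0.29; 0.56 − 0.26) and 0.21–0.24 with Storey (0.56 − 0.35; 0.56 − 0.32). It shrinks at 10% and largely or wholly disappears at 20%. The direction is firm for a 5% or 10% FDR; the size depends on choices the article does not state. The claim that 125 subjects are sufficient goes beyond the calculation, whose own lower end is 0.56 before adjustment.

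**What to change.** Choose one of two routes in Sections 2.8 and 2.8.2.

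1. Name three-year change in sBP as the single primary outcome, tested at two-sided 0.05 outside the q-value family, and keep q-values for all other outcomes. The 0.56–0.80 then stands as printed.
2. Keep sBP in the family, label 0.56–0.80 as unadjusted, and add the sBP power under the planned q-value rule, stating the FDR level, the q-value estimator and the number of outcomes.

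In either case, state in Section 2.8.2 the significance level and group split behind the figure. In Strengths and Limitation, replace the sufficiency claim with the actual power: 0.56–0.80, unadjusted, for a difference of 4.5–6 units over three years, adding under route 2 that it is lower after multiplicity control at the stated FDR level.

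The cost is wording and, for route 2, one run of the power simulation. No participants or measurements are added.

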## 3. Discussion

This study will be one of very few studies investigating relationships between shift work with long working hours and night work and early manifestations of cardiovascular disease in an occupational setting [38,39,40]. We will be doing this prospectively, using a comprehensive and partly novel set of methods. Furthermore, the three implemented investigations regarding plant shutdown, sleep monitoring, and PA-intervention will provide additional knowledge on important aspects of the investigated association between of shift work and cardiovascular health.

Systemic inflammation may contribute to the development of various manifestations of CVD [41]. The development and progression of atherosclerotic CVD is very complex, and has several different stages involving a range of inflammatory agents [42]. Abnormal levels of several pro- and anti-inflammatory agents have been linked to increased risk of developing CVD; these include CRP, MCP-1, TNF-*α*, Il-6, CD40L, and *p*-selectin [43,44,45]. Thus, these markers will provide information on our participant’s CVD risk and progression of risk during the follow-up. Further, we will investigate endothelial dysfunction in the arterial wall by measuring the stiffness of the arteries and through ultrasound of the cIMT. These are noninvasive methods used as proxies for atherosclerosis, and thus, predictors of future CVD. As for cIMT, in a normal, healthy male, one would expect the yearly progression of thickening to be approximately 0.012–0.015 mm [46]; an increase in cIMT of 0.1 mm would increase risk of myocardinal infarction by 10–15 percent and stroke by 13–18 percent [47]. Therefore, this measure provides highly relevant information regarding CVD development. To our knowledge, few research studies within occupational medicine have investigated cIMT. Fujishiro et al. found an increased cIMT thickness in manual workers with low job control [48], while others suggested that shift-work accelerated the atherosclerotic process and was associated with subclinical CVD [40,49]. A high central blood pressure, pulse pressure, augmented pressure, index, and PWV reflect arterial stiffness, i.e., s the load put on the left ventricle and coronary and cerebral vessels. This is a measure shown to have better predictability of cardiovascular outcomes than standard brachial measured blood pressure [50,51,52], and is also a predictor of various other organ disorders and mortality [53]. The recording of central blood pressure and PWV in this study will enable us to investigate possible differences in arterial stiffness between groups and its change during the follow-up.

### Strengths and Limitation

A major strength of this study will be the comprehensive set of health measures and biomarkers used. These measures will provide in-depth information on the participating individual’s cardiovascular health, and improve knowledge on the cardiovascular health effects of shift work with night work and long working hours. The comprehensive set of biomarkers are relevant to a wide range of globally-challenging diseases, and for several of these measures, there is no or limited knowledge on their relationship to shift work.

Another strength is the controlled environment in this study, providing a detailed description of the shift organization, work hours, and sleep status of an individual level. We additionally measure factors as respirable dust exposure and physical activity, both linked to CVD risk factors [54,55], in order to gain control over other aspects which are potentially important in CVD development. This will enable us to better study effects of shift work on early manifestation of CVD.

The three-month shutdown at plant B within our study period will provide us with the opportunity to investigate whether there are any detectable changes in parameters of cardiovascular health connected to this period where participants are not exposed to shift work. In addition, the eight-week HIIT intervention carried out by the Occupational Health Service will provide great information on the effects of PA on the parameters of cardiovascular health, and additionally, will allow us to investigate the mediating effect of PA on the relationship between shift work with long working hours and CVD risk factors.

The prospective design is favorable, and three years is a considerable follow-up time. However, the development of e.g., cIMT is a slow process, and even though changes in cIMT were found in diabetes and coronary patients after a 12-month exercise program [56], the follow-up period may be too short to detect changes, even for subjects in a worsening state. Additionally, at the time of our investigation, many of the workers will have several years of shift work behind them, which may have, in addition to a “healthy worker effect”, an impact on further changes in some of our measures. Thus, we will strive to account for seniority in shift-work in our analyses. There is also a possibility that males and females respond differently to the circadian misalignment occurring during shift work [57], and we will strive to account for this in our analyses. However, we do not aim to investigate this issue separately in our study, and it is unlikely that we will have the optimal data set to do so, considering the male domination of workers in this occupational sector. With a follow-up period of three years, we cannot ignore the possibility of drop-outs during this part of the project. It is also of importance that participants in subgroups of PA intervention and sleep monitoring stay motivated throughout the periods of intervention and continuous measurement. Designated motivators and the involved physiotherapist from the occupational health service will be present during exercise sessions and in regular contact with all the participants. There will also be regular meetings between representatives from the participating enterprises and the project group during the three-year follow-up. This could improve compliance and limit loss to follow-up. From the sample size calculations, we regard a total sample size of 125 subjects as being large enough to show effects, even when considering a reasonable drop-out of participants.

## 4. Conclusions

This project will provide new knowledge on the relationship between one of the largest contributors to death and disability in Norway, and occupational exposure to several consecutive long shifts and night work. This knowledge has the potential to affect how work in these types of work sectors is organized, and potentially prevent or minimize detrimental health effects. It is further plausible that the study findings can be generalized to other parts of the general population.

## Figures and Tables

**Figure 1 ijerph-17-00589-f001:**
[figure not shown]
Time line for data collection.

**Table 1 ijerph-17-00589-t001:** A standard five-week shift plan for Plant A and B.

	Week 1							Week 2							Week 3							Week 4							Week 5						
Weekday	1	2	3	4	5	6	7	1	2	3	4	5	6	7	1	2	3	4	5	6	7	1	2	3	4	5	6	7	1	2	3	4	5	6	7
Plant A			E	E	E				N	N			D	D	E	E	N	N				D	D	D	D	D							N	N	N
Plant B	D	D	D	D					N	N	N	N					E	E		N	N	N				D	D	D	E	E					

D = Dayshift, E = Evening shift, N = Nightshift. Yellow color = 8 h duration of shift, Red color = 12 h duration of shift.

**Table 2 ijerph-17-00589-t002:** The shift plan for Plant B during the nine months prior to plant shutdown and the standard shift plan they return to after reopening.

	Week 1							Week 2							Week 3							Week 4							Week 5						
Weekday	1	2	3	4	5	6	7	1	2	3	4	5	6	7	1	2	3	4	5	6	7	1	2	3	4	5	6	7	1	2	3	4	5	6	7
Before			N	N	N			D	D				D	D			D	D	D			N	N				N	N			N	N	N		
After	D	D	D	D					N	N	N	N					E	E		N	N	N				D	D	D	E	E					

D = Dayshift, E = Evening shift, N = Nightshift. Yellow color = 8 h duration of shift, Red color = 12 h duration of shift.

## Abbreviations

BMI	Body mass index
CD40L	CD40 ligand
cIMT	Carotis intima media thickness
CRP	C-reactive protein
CVD	Cardiovascular disease
dBP	Diastolic blood pressure
EDTA	Ethylene diamine tetra acetic acid
HbA1c	Glycosylated hemoglobin
HDL	High-density lipoprotein
HIIT	High intensity interval training
HR	Heart rate
HRV	Heart rate variablity
IL-6	Interleukin-6
LDL	Low-density lipoprotein
MCP-1	Monocyte chemoattractant protein-1
sBP	Systolic blood pressure
RPM	Revolutions per minute
TNF-*α*	Tumor necrosis factor-alpha
VO_2max_	Maximal oxygen uptake
PA	Physical activity
PAI	Personalized Activity Intelligence
PWV	Pulse wave velocity
